##### Critical flicker-fusion frequency

2.9.2.3

CFF testing will be performed on both eyes using a CFF monitor, following the manufacturer’s instructions (53, 54). The test involves a discontinuous light stimulus fixed in the fovea binocular of the apparatus, and then the frequency of the target gradually increases until participants perceptually perceive the fusion (ascending frequency) or gradually decreases until they identify the visual flicker (descending frequency). Both ascending and descending trials are taken in duplicate to determine the mean threshold frequency.

##### Reaction time

2.9.2.4

Reaction time testing is a quantitative method for assessing the speed and precision of visual processing systems (55). It is conducted with simple reaction time (SRT) and choice reaction time (CRT), following a standardized procedure by trained experienced investigators. The SRT task involves a participant who is instructed to press a button as quickly as possible when a visual stimulus is displayed at a random location on the screen of a specific device. The CRT test involves the visual stimuli of simple graphics presented on the linear light array. The participants are asked to respond correctly to match the stimulus as quickly as possible. The mean RTs of 40 test trials are recorded in milliseconds for each participant.

##### Visuognosis persistence

2.9.2.5

A visuognosis persistence test is widely used to evaluate eye fatigue published by the China Food and Drug Administration (23). In brief, the subjects are instructed to stare at the cubes in a 3-dimensional block diagram at a distance of 1.5 m for 3 min. Unclear vision is defined as inverted cubes. Visuognosis persistence is calculated as the clear vision time divided by the total duration of gaze.

##### Dry eye symptoms and signs

2.9.2.6

Severity of DED symptoms will be assessed using the Ocular Surface Disease Index (56), which consists of 12 items about DED in 3 categories: eye symptoms, visual-related function, and environmental stimulus factors, and ranges from 0 to 100, with higher scores denoting higher severity. This scale has been widely used in the general population and has been shown to be a valid and reliable instrument, appropriate for evaluating the subjective impact of ocular dryness and irritation symptoms on daily life. Objective evaluation of ocular surface condition will be measured for left and right eyes using Keratograph 5 M 77000 (Oculus Corporation, Germany), as described elsewhere (57). The first tear break-up time, average tear break-up time, tear meniscus height, meibomian gland function, and corneal and conjunctival fluorescein staining will be collected by the trained ophthalmologist.

##### Retinal thickness

2.9.2.7

Retinal morphology will be assessed with OCT TR-KT-2736 (optical coherence tomography; Heidelberg Engineering Corporation, Germany), a noninvasive imaging technique that enables optical biopsy *in situ* and in real time, as described elsewhere (58, 59). Participants are seated with their head fixed at the designated position of the instrument, and are instructed to stare at the gaze target for about 10 s. Macular retinal thickness (mRT) is acquired within a volume of the macular cube 512 × 128, and ETDRS grid is used to extract the mRT corresponding to the 9 macular subfields: fovea centralis, four quadrants (superior, nasal, inferior, temporal) with radii of 1–3 mm and 3–6 mm around fovea (the inner ring and outer ring). Mean macular retinal nerve fiber layer thickness, the thickness of the retinal ganglion cell layer, and inner plexiform layer in four quadrants (superior, nasal, inferior, temporal), and retinal volume are extracted from color maps generated by the OCT software. Thirty minutes after pupil dilation with 0.5% tropicamide and 2.5% phenylephrine, OCT scans will be performed separately for each eye by an experienced ophthalmologist.

##### Optical quality

2.9.2.8

Information regarding accommodative ability will be obtained with the double-pass retinal images of the OQAS II (the Optical Quality Analysis System; Visiometrics Corporation, Spain), including strehl ratio, modulation transfer function (MTF) cutoff frequency, object scatter index and the OQAS values. Refractive errors, corneal curvature, pupil diameter, and MTF are determined using an OPD-Scan III unit (Nidek Corporation, Japan). Images will be automatically captured and recorded on the system through a strict quality control of assay performance. All examinations are performed for each eye by an impartial ophthalmologist using standard operating procedures.

#### Blood samples and serum carotenoid levels

2.9.3

Fasting venous blood samples will be obtained by trained nurses or phlebotomists. Two vials of whole blood will be collected from each participant: (1) 5 mL into EDTA-containing tubes; (2) 5 mL into vacutainer tubes containing clot activator. Blood samples from vial 1 are centrifuged at 3500 *g* for 15 min at 4°C within 30 min after being drawn for separating plasma, buffy coat, and red blood cells (RBCs). Blood samples from vial 2 are allowed to sit at room temperature for 60 min to coagulate, and then centrifuged at 3500 *g* for 15 min at 4°C for separating serum. The resultant samples are aliquoted in 1.5 mL well-labeled tubes, and stored at −80°C in the biobank of the Xi’an Jiaotong University until assay.

Measurements of serum concentrations of lutein, zeaxanthin, *β*-cryptoxanthin, *α*-carotene, *β*-carotene, and lycopene will be performed at the key laboratory using a reversed-phase high performance liquid chromatography (HPLC) system equipped with a YMC-carotenoid C30 analytic column (250 mm × 4.6 mm × 5 μm; YMC Corporation, Japan), as previously described (60). Cryopreserved serum aliquots are thawed in a subdued light container at room temperature. Processing of the sample involves precipitation by 250 μL of mixed internal standard solution (methanol: acetonitrile = 1:2, v/v) containing 5 μL of echinenone, dryness of the aggregate supernatant under nitrogen gas, and reconstitution by 100 μL of methanol after drying the extracts. The mobile phase is methanol (A), and isopropyl: n-hexane (1:1, v/v) (B) with a gradient elution program of 0–50% (B) in 0–20 min, 50–100% (B) in 20–30 min and then re-equilibration of the column with 0% B for an additional 8 min. The injection volume is 10 μL at a flow rate of 1 mL/min, and the column temperature is kept at 15°C. Chromatograms are evaluated at 450 nm for carotenoids by using purified external standards. Concentrations are derived using eight-point standard addition calibration curves in the range of 0.005–50 μg/mL. Quality control samples at three concentrations (low, medium, and high) are prepared for method validation.

#### Erythrocyte membrane omega-3 fatty acids

2.9.4

The omega-3 fatty acids content of RBC membranes will be measured at the central medical laboratory by using gas chromatography (GC) technique equipped with an SP-2560 fused-silica capillary column (100 m × 0.25 mm × 0.2 μm; Shimadzu Corporation, Japan) following published methods (61–63). A typical procedure will be used for the preparation of red blood cell (RBC) membrane samples as follows: the 200 μL membrane suspension is mixed with hexane and isopropanol (2.5 mL; 3:2, v/v) containing 15 μL of eicosanoic acid methyl ester as an internal standard, and then blended sufficiently. After centrifugation, the supernatant is collected and taken to dryness under a vacuum concentration system. The dried residue is methylated with methanol and acetyl chloride (25 mL; 4:1, v/v) and then heated at 95°C for 1 h. After cooling, the sample is mixed with 2.25 mL of 48% K_2_CO_3_, and the combined supernatant is dried down under nitrogen. The resultant fatty acid methyl esters (FAMEs) are solubilized in 80 μL isooctane and 20 μL is injected into the GC system. The oven temperature is 170°C for 5 min, increased to 175°C at a rate of 5°C/min, then increased 1°C/min up to 210°C, held for 5 min, followed by a final increase of 5°C/min up to 240°C, held for 20 min. DHA and EPA are identified by comparing their peak retention times with a standard mixture of FAMEs and expressed as relative percentages of total fatty acids. A series of quality control assays are performed to determine the data repeatability.

#### DNA extraction and genome-wide genotyping

2.9.5

High quality DNA samples will be purified from the buffy coat using the Genomic DNA Extraction kits according to the manufacturer’s instructions. Genome-wide genotyping will be carried out using the Affymetrix Axiom^®^ Array Automated Workflow, following the manufacturer’s protocol (64, 65). DNA stock solutions are amplified and fragmented into base pair fragments. These fragments are purified, resuspended, and then hybridized to Affymetrix Axiom^®^ Arrays. Hybridization, ligation, washing, staining, and scanning are automatically processed on the GeneTitan Instrument (Affymetrix). Finally, the genotypes of total genomic DNA for each sample are obtained through the Genotyping Console program (Affymetrix). Data management is performed on a High Performance Computing cluster. Quality control filters are applied to study samples and genotyping (e.g., genetic sex matching self-reported sex, per-sample missing rate < 10%), single nucleotide polymorphisms (SNPs) with minor-allele frequency > 1%, SNPs with a genotyping success rate of ≥95%, and Hardy–Weinberg Equilibrium *p*-value >1 × 10^−6^.

#### Fecal sample collection and 16S rRNA gene sequencing

2.9.6

Stool samples are obtained by participants themselves using stool collection kits following a detailed description of sample collection instructions. All samples are immediately transferred to −80°C freezer using an insulated foam box filled with ice within 2 h of collection until subsequent analysis of intestinal microbial composition.

Total microbial DNA will be extracted from each fecal sample using the Stool DNA Purification Kit in accordance with the manufacturer’s instructions. The V3 to V4 region of the bacterial 16S ribosomal RNA (rRNA) gene will be amplified via the polymerase chain reaction technique using primers with unique barcodes (338F and 806 R), High-throughput sequencing of the amplified products is performed utilizing an Illumina MiSeq sequencer (66). The quality filtering of raw sequences and operational taxonomic units (OTUs) clustering are conducted by the Quantitative Insights into Microbial Ecology (QIIME) platform following the standard operating procedure. All effective paired-end reads from each sample are assigned to the same OTUs based on a 97% identity threshold. Metrics of alpha diversity, including the standard Shannon and Simpson diversity indices and richness indices (the abundance coverage-based and the Chao1 estimator) will be calculated based on the rarefied OTU counts. Principal component analysis and principal coordinate analysis are performed to evaluate the beta diversity of bacterial flora in samples.

#### Covariates

2.9.7

Information on contact details (name, phone number, and place of residence), demographics (age, sex, educational attainment, employment, parental education, and household income), daily screen time of near-field technological devices (smartphones and computers), reading habits (the use of a table lamp, reading distance, and performing eye exercises), sunlight exposure (residence calendar, employment history, time spent outdoors during work and leisure activities, and hat and eyeglass use), lifestyle behaviors (smoking, alcohol consumption, the use of antioxidant supplement, physical activity, and sleep quality), family history (cardiovascular disease, diabetes mellitus, myopia, glaucoma, cataract, and AMD), and menstruation will be collected using standardized questionnaires by trained fieldworkers. Screen time utilization and the use of electronic devices in a dark environment at night, will be evaluated by the time spent on smartphones and computers on typical weekdays and weekends. The mean daily screen time will be calculated using the formula: (5 × hours of screen time on weekdays +2 × hours of screen time on weekends)/7. The validity of the questionnaires in measuring smartphone use was evaluated by comparing with data from the preinstalled application located in the smartphone’s settings in a subsample of the participants in this trial (*n* = 30). Correlation coefficient between subjective and objective measures was 0.55 for daily smartphone use. The ocular ambient exposure to different wavelengths of light will be constructed on the basis of detailed exposure histories and published ambient data. Participants will be asked to provide information on residential history, work history, the average time spent outdoors during daylight hours for different occupational and leisure periods in winter and summer, and the proportion of hat and eyewear (glasses, contact lenses, and sunglasses) use after the age of 15 years (67, 68). Ambient data will be obtained from the National Aeronautics and Space Administration Goddard Earth Sciences Data and Information Services Center (69), which provides data on erythemally weighted daily dose of ultraviolet (UV, J/m^2^), UV index, and noontime spectral irradiances at four wavelengths (305, 310, 324, and 380 nm). Geographical coordinates of each location are used to assign the daily ambient exposure levels to each subject. Blue light (400 to 500 nm) in the visible spectrum will be estimated using the tropospheric ultraviolet and visible radiation transport model (70). Yearly ocular exposure to each wavelength of light will be quantified using an adaptation of the mathematical model developed by Rosenthal et al. (71), by summing the daily fraction of ocular exposure during work and leisure hours. The daily fractions of ambient radiation reaching the eye are determined from ambient exposure at each place, the time spent at that location, the ocular ambient exposure ratio, and attenuation factors provided by ocular protection (72, 73). Finally, a cumulative ocular exposure is calculated as the sum of the yearly exposures. Physical activity will be assessed using a validated International Physical Activity Questionnaire (74). Subjective sleep quality will be evaluated by a validated Pittsburgh Sleep Quality Index (75).

#### Anthropometry

2.9.8

Anthropometry will be measured in triplicate by trained staff and the average reading is recorded. Systolic and diastolic blood pressure are measured in a seated position after 10 min of resting using an automated digital device (Omron Corporation, China). Body weight and composition are measured without shoes by bioelectrical impedance using a calibrated BC-582 digital scale (Tanita Corporation, China). Body mass index (BMI; in kg/m^2^) is calculated as kilograms (kg) of weight divided by the squared height in meters (m) and categorized as “underweight (<18.5 kg/m^2^),” “normal weight (18.5–24.9 kg/m^2^),” “overweight (25–29.9 kg/m^2^),” and “obese (≥30.0 kg/m^2^),” defined by World Health Organization described by Global BMI Mortality Collaboration (76). Waist circumference will be assessed at the umbilicus to the nearest 0.1 cm using a non-elastic measuring tape.

#### Dietary assessment

2.9.9

Dietary intake is assessed using a semi-quantitative food frequency questionnaire (FFQ) by trained research staff to collect information on the consumption frequency in standard portion sizes of each food item over the previous year. The FFQ consists of 105 food items which are assembled into 12 categories: cereals; vegetables; legumes and soybean products; mushrooms and seaweeds; fruits; nuts; egg, meat and processed meat; milk and dairy products; beverages; snack foods and confectionaries; oils; and condiments. Participants will be requested to choose from nine predefined categories of preidentified foods as follows: “never or less than once per month”; “1–3 times per month”; “once a week”; “2–4 times per week”; “5–6 times per week”; “once per day”; “2–3 times per week”; “4–6 times per week”; and “6 or more times per day.” Consumption frequencies are converted into the daily intake frequencies of the given food item using the midpoint of frequency options. Daily intakes of energy and nutrients are computed by multiplying the daily intake of each food item (g/d) with the relevant nutrient in specified portions (100 g), summed across all foods consumed. The reproducibility and validity of this FFQ have been documented in previous studies performed by our research group (77).

### Safety assessments

2.10

A safety assessment including adverse events (AEs) and concomitant medications will be conducted from baseline until the final visit or early withdrawal. AEs are defined as any untoward medical occurrence among participants, which are not necessarily associated with supplement use. Participants will be advised to report any unfavorable and unintended symptom, sign or disease to the research assistant as soon as they can by e-mail or telephone during the intervention. In addition, abnormal findings considered clinically significant by a medical staff will be also recorded as an AE. Serious adverse events are defined as any untoward medical occurrence that caused hospitalization, significant incapacity or permanent damage, and any other serious medical condition requiring medical or surgical intervention. Information regarding the course of AEs, including description, date of onset, duration, actions taken, and outcome, is registered using a standardized form and evaluated for severity and causal relation to the study treatment by a medical investigator.

### Data management and confidentiality

2.11

Data management and confidentiality will be performed by the Xi’an Jiaotong University Health Science Center. At enrollment, proper measures will be taken by keeping the identity of the participant anonymous by replacing their full names and contact details with a unique number. Data collection forms in paper-based format will be securely stored in a locked cabinet with restricted access only to designated study members. Survey questionnaires will be completed and stored electronically in the Research Electronic Data Capture (REDCap) system, an online secure data management system hosted by the Xi’an Jiaotong University. REDCap servers are encrypted and accessible only by authorized personnel. In some cases, representatives from BYHEALTH Co., LTD and Xi’an Jiaotong University Health Science Center will review the accumulating data for the purposes of monitoring safety and quality of data and the fidelity of statistical analysis.

### Statistical analysis

2.12

Analysis of the primary and secondary outcomes will be conducted following the intention-to-treat (ITT) principle, whereby participants will be included in the groups to which they were originally assigned, irrespective of compliance or loss to follow-up. Missing values on baseline covariates and follow-up data will be imputed by multiple imputation methodology (78). Investigators and participants remain blinded to treatment assignment during the trial. No interim analysis is planned.

Normally distributed values will be assessed and verified using the Shapiro–Wilk test. Descriptive summaries of quantitative variables include means and standard deviations for normally distributed variables and interquartile ranges for nonnormal variables. Categorical variables are presented as frequencies and percentages. Baseline characteristics of each arm will be compared by the two-sample t-test, one-way analysis of variance (ANCOVA) and the Wilcoxon rank-sum test for continuous variables, and chi-squared test for categorical variables.

Change in continuous outcomes at each time point will be calculated as follow-up minus baseline and be represented as the mean change and 95% confidence intervals. Change in primary and secondary outcomes from baseline at 24 weeks between study arms will be performed using ANCOVA adjusted for potential covariates. Paired t test and Wilcoxon signed-rank test will be conducted for normally and non-normally distributed data, respectively. Linear mixed effects models will be performed to evaluate differences in outcome changes over time (e.g., baseline, 12, and 24 weeks) between the intervention and control groups, with the baseline values of corresponding outcomes, stratifying variables and time-group-interactions as covariates. Multiplicative interaction terms in linear mixed effects models are used to explore interactions between genetic variations or gut microbiota and the intervention outcomes.

Sensitivity analyses will be performed to verify the robustness of the results by converting continuous outcomes into categorized values and using generalized estimating equations comparing the risk ratio between groups. Subgroup analyses will be conducted to assess the moderation of the effects of randomized intervention groups by the baseline covariates (e.g., sex, time spent outdoors, ocular exposure to ambient UV radiation, blue light exposure, screen time of digital devices, or dietary carotenoid intake).

Statistical analyses are performed using SPSS statistical package version 22.0, and R version 3.4.0 (e.g., the lme4 package, and the lmerTest package), and a two-sided *p* ≤ 0.05 will be used to determine statistical significance.

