### Sample size calculation

2.4

The sample size calculation was determined by assuming a > 20% increase in MPOD change between the intervention arms receiving lutein and zeaxanthin supplementation and the placebo (19), if a 2-sided type I error and statistical power were set as 5 and 80%, respectively. A total of 75 participants should be recruited in each arm. Accounting for 20% potential dropouts, a minimum of 94 participants per group would be needed. Finally, the number of enrolled participants was determined to increase to 100 in each group (600 for 6 groups) for an adequate sample size.

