### Follow-up procedures

2.7

A total of three follow-up visits will be scheduled at baseline (prior to randomization), 12 weeks (secondary time point), and 24 weeks (primary time point). At enrollment, potential participants will be invited to the research center to provide informed consent and complete a screening questionnaire on demographic characteristics and health status, including information on lifestyle behaviors, preceding medical diagnoses as well as medications and dietary assessment. After successful completion of initial questionnaire screening, a routine clinical examination, including a physical examination and a comprehensive ophthalmic examination, will be performed in the hospital to further confirm their eligibility. Anthropometric measurements (e.g., height, weight, and waist circumference), evaluation of MPOD and visual function, and collection of biological samples (fasting blood and feces) will be fitted to each individual at the same time. At the 12-week visit, participants are asked to complete the follow-up questionnaire to provide update information on health status, and undertake assessments of MPOD and visual function. At the end of the 24-week supplementation period, they will be invited to return the research center, and scheduled to visit the hospital for repeated measurements. Fasting blood samples will be collected, and concentrations of serum lutein and zeaxanthin, and red blood cell (RBC) membrane omega-3 fatty acids will be measured at each study visit. Genome-wide genotyping will be assessed at baseline. Gut microbiota profiles will be performed for all fecal samples collected at baseline and the 24-week follow-up visit. The study staff will make regular telephone calls to participants to confirm their health condition and medication adherence. The time schedule of enrollment, interventions, assessments, and follow-up for participants is described in Figure 1 (flow chart of the clinical trial) and Table 2 (enrollment, interventions, and assessments).

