### Primary and secondary outcomes

2.8

The primary outcome is the change in MPOD over the course of the trial. Secondary outcomes include the change in the comprehensive test battery for visual function [best-corrected visual acuity (BCVA), CS, GS, critical flicker fusion (CFF), reaction time, visuognosis persistence, in-depth assessment of dry eye disease (DED) diagnosis and symptomatology, retinal thickness, and optical quality], changes in the concentrations of serum lutein and zeaxanthin, and erythrocyte membrane omega-3 fatty acids at each time point, the compositional changes in the intestinal microbiota before and after supplemental intake of lutein, zeaxanthin, and omega-3 fatty acids, and determination of whether changes in primary and secondary outcomes are associated with genetic variations, baseline microbiome characteristics, and changes in intestinal microbiota.

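### Section 2.12 imputes all missing follow-up data and does not exempt the gene, microbiome and subgroup interaction tests, so any interaction left out of the imputation model is pulled toward zero

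*Protocol article*

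**What the plan says.** All references are to the protocol article.

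- Section 2.12 opens with its scope: "Analysis of the primary and secondary outcomes will be conducted following the intention-to-treat (ITT) principle". The missing-data rule follows directly: "Missing values on baseline covariates and follow-up data will be imputed by multiple imputation methodology (78" (the number is a literature citation).
- Two paragraphs later the section sets the effect-modification tests: "Multiplicative interaction terms in linear mixed effects models are used to explore interactions between genetic variations or gut microbiota and the intervention outcomes". It adds: "Subgroup analyses will be conducted to assess the moderation of the effects of randomized intervention groups by the baseline covariates", with six example moderators (sex, outdoor time, UV exposure, blue light, screen time, dietary carotenoids).
- Section 2.8 puts effect modification among the secondary outcomes: "determination of whether changes in primary and secondary outcomes are associated with genetic variations, baseline microbiome characteristics, and changes in intestinal microbiota". On a plain reading, the imputation rule therefore covers these tests.
- Section 2.7 sets the scale of the genetic data: "Genome-wide genotyping will be assessed at baseline". Section 2.9.5 names a genome-wide array, and section 2.9.6 plans 16S sequencing.
- Section 2.4 gives the only planning figure for missing data: "Accounting for 20% potential dropouts, a minimum of 94 participants per group would be needed".
- Table 2 schedules MPOD and most visual tests at baseline and weeks 12 and 24. Dry eye, retinal thickness, optical quality and stool sampling have no week-12 visit.

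**The concern.** Imputed outcomes follow the model that generated them. If that model has no arm-by-marker term, and no predictor that reflects one, the imputed participants show no effect modification. Pooling them with the observed participants dilutes the estimate.

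The usual remedy is to put every tested interaction in the imputation model. That works for a few moderators but not for many SNPs or taxa in one model for 600 people.

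Who responds to supplementation is a stated aim in the Abstract, Introduction and Discussion. A bias toward no modification matters because a null result could partly reflect the missing-data rule. Interaction tests with about 100 people per arm have little power to spare.

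The microbiome analysis has a further difficulty. Stool is collected only at baseline and week 24, so someone who misses week 24 lacks both the outcome and the microbiome change it is to be related to.

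**Working it through.** **1. The plan's own figure.** Section 2.4 starts from 75 per arm and allows 20% dropout: 75 / (1 − 0.20) = 93.75, rounded up to 94. This matches. The 20% is used below as a stand-in for the fraction f imputed at week 24. The article gives no figure for interaction attenuation.

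**2. Expected shrinkage when the interaction is omitted from the imputation.** Let s be the share of the week-24 interaction already present at week 12, and ρ the residual correlation between weeks 12 and 24. Neither is in the article.

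- No week-12 value in the imputation: estimate / truth ≈ 1 − f. For f = 0.20 this is 0.80; for f = 0.10 it is 0.90.
- Week-12 value in the imputation for every dropout: estimate / truth ≈ (1 − f) + f·ρ·s. At f = 0.20:
  - ρ = 0.7, s = 1.0: 0.80 + 0.20 × 0.70 = 0.94
  - ρ = 0.7, s = 0.6: 0.80 + 0.20 × 0.42 = 0.884
  - ρ = 0.5, s = 0.6: 0.80 + 0.20 × 0.30 = 0.86

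**3. Simulation.** Assumptions: two arms of 100; true interaction 0.6 SD (per allele at allele frequency 0.3, or between the levels of a binary moderator); ρ from 0.5 to 0.7; s from 0.6 to 1.0; outcomes missing completely at random; 10 imputations; Rubin's rules; 1,500 runs per scenario.

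| Handling of missing outcomes | Estimate / truth, 20% missing | Estimate / truth, 10% missing | Power, SNP scenarios, 20% missing |
|---|---|---|---|
| Imputed, interaction and week 12 both omitted | 0.79–0.82 | 0.89–0.91 | 0.46–0.49 |
| Imputed, interaction omitted, week 12 used | 0.85–0.97 | 0.92–0.99 | 0.56–0.69 |
| Imputed, interaction included | 0.99–1.03 | 0.99–1.01 | 0.65–0.71 |
| Complete cases, no imputation | 1.00–1.03 | 0.99–1.01 | 0.66–0.68 |

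The simulated ratios agree with step 2. The 0.97 comes from a scenario in which even the correct imputation read 1.025, so the 3% end of the loss range is partly simulation noise.

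**4. No true interaction, 20% missing.** Rejection rate at the 5% level: about 0.02 with the interaction and week 12 omitted, 0.03 with only the interaction omitted, and 0.05 with it included.

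**5. The proposed alternative.** A separate simulation used 0.45 SD per allele, allele frequency 0.3 and 20% missing completely at random. Imputation without the term gave 80–95% of the true interaction and 26–44% power. A likelihood fit to the observed visits gave 98–101% and 42–50%. Another run at the same effect size gave 84%, 82% and 80% of truth when all, half or none of the dropouts had a week-12 value. By the formula in step 2, 0.84 corresponds to ρ·s = 0.20, so a weaker link between visits moves the loss toward 20%. Absolute power is specific to each simulation's assumptions; only the contrast within each should be read.

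**6. Can one imputation model hold the terms?** With six arms and additive coding, each marker needs 1 main effect and 5 arm interactions, so 6 coefficients. With 20% missing, 600 × 0.80 = 480 week-24 values are observed. An ordinary regression imputation is saturated at 480 / 6 = 80 markers, before any other predictor enters.

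**The case against.** The strongest objection is that the faulty step is not written down. The article does not say that one common imputation is used, that interactions are left out of it, or that the interaction mixed models run on imputed data. Section 2.12 names lme4, which fits by likelihood and can be run on available visits. The contents of an imputation model are commonly left to an SAP. This stands, and it makes the shrinkage conditional. What remains is that the article states an unqualified rule covering secondary outcomes and exempts nothing.

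A reader might infer four stronger points, which the documents do not support:

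- *Every true interaction is shrunk by the imputed fraction.* The six example moderators, or a short list of candidate variants, can go in the imputation model, and the loss then disappears. The imputed fraction behaves as an upper bound, and week-12 data reduce the loss.
- *A genome-wide interaction scan is planned.* Genome-wide genotyping is a measurement. The Introduction speaks of variation at specific genes, and section 2.12 calls the interaction tests exploratory. Candidate analyses are still affected if the tested term is omitted.
- *The rule creates false findings or harms the primary comparison.* Step 4 shows a conservative test, and the main-effect comparison is not at issue.
- *Imputation adds nothing to a mixed model.* It can use auxiliary variables and fill missing baseline covariates, which an outcome-only likelihood fit cannot.

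The alternative also has a cost: it leaves some randomized participants out of the interaction analyses, although section 2.12 promises inclusion irrespective of loss to follow-up.

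**Conclusion.** The concern holds conditionally, as a cheap improvement. On its plain reading, section 2.12 runs the interaction tests on imputed outcomes, and any interaction missing from the imputation model is attenuated. At 20% missing the loss is about 3 to 15% when every dropout has a week-12 value that the imputation uses, and about 20% when none does. The second case applies to dry eye, retinal thickness and optical quality, and to anyone lost before week 12. The consequence is lost power in exploratory tests: in the SNP scenarios, 0.46–0.49 against 0.65–0.71 in the worst case.

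These sizes rest on assumed interactions, correlations and allele frequency, on two arms, and on data missing completely at random. Other missingness patterns could change them. The 20% is a planning allowance and not an observed fraction.

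**What to change.** Add to section 2.12, in substance: the arm-by-gene and arm-by-microbiome interaction mixed models are fitted by likelihood to the observed visits, with no imputed outcomes or microbiota; for the named subgroup moderators, either the same approach is used or imputation is done separately by arm with the moderator in the imputation model. Keep multiple imputation for the week-24 main-effect ANCOVA as planned.

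The cost is one sentence and less computing, since the mixed models are already planned. Under missing at random the likelihood fit needs no imputed outcomes. The downside should be stated in the plan: participants with no post-baseline value for an outcome do not contribute to its interaction analysis, and for outcomes without a week-12 visit this is a complete-case analysis.
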